# Point of care testing for urinary tract infection in primary care (POETIC): protocol for a randomised controlled trial of the clinical and cost effectiveness of FLEXICULT™ informed management of uncomplicated UTI in primary care

**DOI:** 10.1186/s12875-014-0187-4

**Published:** 2014-11-25

**Keywords:** Urinary Tract Infection, Primary care, Adult women, Point-of-care-test, Near-patient testing, Antibiotic resistance, Cost effectiveness

## Abstract

**Background:**

Urinary tract infections (UTI) are the most frequent bacterial infection affecting women and account for about 15% of antibiotics prescribed in primary care. However, some women with a UTI are not prescribed antibiotics or are prescribed the wrong antibiotics, while many women who do not have a microbiologically confirmed UTI are prescribed antibiotics. Inappropriate antibiotic prescribing unnecessarily increases the risk of side effects and the development of antibiotic resistance, and wastes resources.

POETIC is a randomised controlled trial of a Point Of Care Test (POCT) (Flexicult™) guided UTI management strategy for use in primary care, which may help General Practitioners more effectively decide both *whether* or not to prescribe antibiotics, and if so, to select the *most appropriate* antibiotic.

**Methods/design:**

614 adult female patients will be recruited from four primary care research networks (Wales, England, Spain, the Netherlands) and individually randomised to either POCT guided care or the guideline-informed ‘standard care’ arm. Urine and stool samples (where possible) will be obtained at presentation (day 1) and two weeks later for microbiological analysis. All participants will be followed up on the course of their illness and their quality of life, using a 2 week self-completed symptom diary. At 3 months, a primary care notes review will be conducted for evidence of further evidence of treatment failures, recurrence, complications, hospitalisations and health service costs.

The primary objective is to compare appropriate antibiotic use on day 3 between the POCT and standard care arms using multi-level logistic regression to produce an odds ratio and associated 95% confidence interval. Costs of the two management approaches will be assessed in terms of the primary outcome.

**Discussion:**

Although the Flexicult™ POCT is used in some countries in routine primary care, it’s clinical and cost effectiveness has never been evaluated in a randomised clinical trial. If shown to be effective, the use of this POCT could benefit individual sufferers and provide evidence for health care authorities to develop evidence based policies to combat the spread and impact of the unprecedented rise of infections caused by antibiotic resistant bacteria in Europe.

**Trial registration number:**

ISRCTN65200697 (Registered 10 September 2013).

## Background

Each year, about 10% of adult women experience a urinary tract infection (UTI) and about 60% experience a UTI at some point in their lives [1,2]. Recurrences are common, with nearly half going on to experience a subsequent UTI within a year. UTI accounts for about 15% of antibiotics prescribed in primary care, and between 34% and 60% of patients treated with an antibiotic do not have a microbiologically proven UTI and 25% of those with a positive urine culture are not prescribed antibiotics.

For those who are likely to benefit, antibiotics have been shown to reduce symptom duration [3]. However, some do not benefit from antibiotics and as these carry risks of side effects, increased antibiotic resistance and costs, unnecessary antibiotic use should be minimised. In a systematic review and meta-analysis of five studies of urinary tract bacteria that included 14 348 participants, the pooled odds ratio (OR) for resistance was 2.5 (95% CI 2.1 to 2.9) within two months of antibiotic treatment and 1.33 (95 % CI 1.2 to 1.5) within 12 months [4].

Antibiotic resistant UTIs are common in primary care, with recent antibiotics the greatest single risk factor for a resistant compared to a sensitive infection [5]. Resistant infections are associated with longer illness duration, increased re-consultations, and increased health care costs [6,7].

Current strategies to predict bacteriological UTI in adult women need refining so that more women who will benefit from antibiotic treatment are prescribed them, antibiotic treatments are better targeted to the sensitivity of the infecting organisms, and antibiotics are prescribed less often for women who will not benefit. There is thus an urgent need to support General Practitioners in deciding both *whether* or not to prescribe antibiotics and, if so in selecting the *most appropriate* antibiotic. Accurate diagnosis and rational treatment is required to minimise acute suffering and help prevent recurrences.

The POETIC trial is an evaluation of a Point of Care Test (POCT) guided UTI management strategy for use in adult women presenting in primary care with suspected uncomplicated UTI. The POCT that will be evaluated is called Flexicult™ and is a simple point of care culture procedure, and provides clinicians, at the point of care, within 24 hours, with a microbiological diagnosis of bacterial UTI by quantifying bacteria in the urine sample (or not) and determining sensitivities of any identified pathogen to the antibiotics most commonly used for UTI in primary care [8].

POETIC aims to determine the clinical effects and costs of this optimised POCT guided diagnostic and treatment strategy for symptoms of uncomplicated UTI on the overall appropriateness of antibiotic prescribing when compared to a “practice based on best available local guidelines” strategy. The POETIC trial will determine whether or not the POCT aids clinicians to more appropriately prescribe antibiotics for uncomplicated UTI’s i.e. minimise the use of antibiotics for women where no bacterial infection is identified, and ensure the narrowest spectrum antibiotic appropriate to the sensitivity of the infecting organisms is prescribed when a bacterial infection is identified, and whether or not the strategy is cost effective.

## Methods/design

### Trial design

POETIC is a two-arm, individual patient randomised controlled trial aiming to quantify the effects and costs of an optimised POCT guided diagnostic and treatment strategy for symptoms of uncomplicated UTI on the overall appropriateness of antibiotic prescribing when compared to a “practice based on best available local guidelines” strategy. The research will be implemented in primary care research networks in the four participating European countries (Wales, England, the Netherlands and Spain).

The trial will randomise 614 eligible women to either the POCT guided management strategy, or to a standard UTI management strategy based on best local guidelines.

### Setting

This multinational trial will be implemented in primary care research networks based in Wales, England, Spain and the Netherlands. Each centre will recruit adult women with symptoms attributable to UTI, over the age of 18 years, from their affiliated primary care sites.

### Trial intervention

Participants randomised to the experimental intervention arm will have their treatment guided by the Flexicult™ POCT. This POCT is a point of care culture-based approach and involves fresh urine being placed on a special agar plate and the excess urine poured off. The plate is then placed in a simple desktop incubator within the practice, and read approximately 24 hours later.

Patients can only be included in the POCT arm if the clinician/nurse is able to read the plate 24 hours later. The plate is divided into six segments. The largest compartment contains culture medium alone, and the other five segments contain culture medium with impregnated with different antibiotics with specific concentrations commonly used for treating UTI in primary care. This allows for assessment of bacterial growth (quantification), evaluation of the species present, and assessment of resistance to the antibiotics in each of the plate segments.

The Flexicult™ system has been used in primary care settings in Denmark for approximately 10 years. POETIC will use new Flexicult™ plates that have been developed by the manufacturer and CE marked (Statens Serum Institut, SSI) to include the antibiotics that are most commonly used in the three participating regions (UK -England and Wales, Spain and the Netherlands) (see Table 1 below):

**Table 1 Tab1:** **Antibiotics included in Flexicult™ plate for each region**

**UK**	**Netherlands**	**Spain**
Trimethoprim	Trimethoprim	Fosfomycin
Nitrofurantoin	Nitrofurantoin	Nitrofurantoin
Amoxicillin/clavulanate	Amoxicillin/clavulanate	Amoxicillin/clavulanate
Ciprofloxacin	Ciprofloxacin	Ciprofloxacin
Cephalexin	Amoxicillin	Cefuroxime

Clinicians will be provided with training in the management of UTI using the Flexicult™ approach. Two treatment approaches will be available to participating clinicians for patients randomised to this arm:Provide patients with advice about symptomatic management of their UTI for approximately 24 hours and arrange a mechanism for contacting the patient in approximately 24 hours in order to arrange provision of a prescription for antibiotics, or not, as appropriate, based on the results of the Flexicult™ POCT test.Provide patients with a prescription for antibiotics to start immediately and arrange a mechanism for contacting the patient approximately 24 hours later in order to advise the patient to continue taking the antibiotics, stop taking the antibiotics, or switch to an alternative antibiotic, as appropriate, based on the results of the Flexicult test.

Clinicians will be encouraged to adopt the first approach for patients with milder symptoms and/or for those that would be happy/would prefer to wait 24 hours for a more definitive diagnosis, and the latter approach for those with more severe symptoms or who are not happy to delay initiation of antibiotics.

### Control arm –standard care

Patients randomised to the control arm will receive standard care informed by national guidelines. Clinicians will receive a summary of national guidelines on the management of uncomplicated UTI in primary care (UK, Spain and the Netherlands). Participating clinicians will be provided with the relevant summary for their country, and training in best practice based on their national guidelines. The management of patients who are randomised to the standard care arm will therefore be based upon the management decisions of clinicians who have received training in best practice and a summary of their national guideline(s). Management decisions in these patients randomised to guideline informed usual care will *not* be guided by the POCT.

### Primary objective

The primary outcome will be appropriate antibiotic use on day 3 (with day 1 being the day that the patient consulted with their primary care clinician). For women who are shown to have a UTI. Appropriate antibiotic use on day 3 will be defined as use of an antibiotic for which the isolated pathogen has been shown to have *in vitro* sensitivity (based on laboratory analysis). For women who do not have a UTI, appropriate antibiotic use on day 3 will be defined as no antibiotic use on this day. In the UK the definition of a UTI is defined for the POETIC trial as ≥10^5^ colony forming units per millilitre (cfu/ml) of a pure/predominant recognised uropathogen, however the varying definitions across the countries will be considered.

### Secondary objectives

The secondary objectives are to compare intervention arms with regard to:Antibiotic choice in relation to presence of infection and organism susceptibility and antibiotic spectrumDose and duration of antibiotic prescribedProportion of patients receiving antibiotic prescriptionAdherence to national prescribing guidelinesSymptoms/recoveryRecurrence of UTI (within a three month period)Patient satisfaction with managementAntibiotic resistance in urine and stool samples at two week follow upDirect/indirect costsCost effectiveness

### Ethical and governance approval

This trial protocol was approved by the Research Ethics Committee (REC) For Wales recognised by the United Kingdom Ethics Committee Authority (UKECA) and also approved by the relevant local Governance Committees in the Netherlands and Spain.

All sites within the UK received Research & Development approval from the appropriate Health Boards and Trusts before commencing trial. For Spain, approval was obtained by the Institut d‘Investigació d’Atenció Primària Jordi Gol i Gurina, Barcelona. For the Netherlands, approval was obtained from Medisch Ethische Toetsingscommissie of the Universitair Medisch Centrum Utrecht (University Medical Center Utrecht).

### Trial procedures

#### Primary care sites/GP practice recruitment

The trial centres have been selected on the basis of having well-established primary care research networks and representing contrasting European cultures and healthcare systems. Each centre will recruit around 10 general practices to participate in the trial. Practices will be selected on the basis of recruitment potential, with larger practices and practices which have previous experience in recruiting participants during routine consultations.

All participating practices will receive face-to-face training with additional online resources, via a bespoke POETIC website (www.POETIC-study.co.uk), in use of the POCT strategy. This will include sample collection and preparation, use of the POCT, interpretation of the POCT results, data collection and storage, health and safety issues and management strategies (how to use the results of the POCT in line with best evidence and local guidelines).

#### Microbiology laboratory recruitment

The participation of any primary care site in recruitment to the trial requires the support and participation of a research microbiology laboratory in each of the participating countries, to which the site sends urine and stool samples for the purposes of the POETIC trial.

For sites in Wales and England, samples will be sent to the Specialist Antimicrobial Chemotherapy Unit (SACU), Public Health Wales Microbiology Cardiff, at University Hospital of Wales. In The Netherlands, samples will be sent to the Department of Medical Microbiology of the Universitair Medisch Centrum Utrecht. In Spain, the samples will be sent to the Microbiological Departments of the Hospitals Ramón y Cajal (Madrid), Joan XXIII (Tarragona), and Bon Pastor (Barcelona). All laboratories will be provided with a POETIC microbiology manual and standard operating procedures.

### Participant recruitment

The recruitment process is summarised in Figure 1.

**Figure 1 Fig1:**
[figure not shown]
**Trial schema and participant flow diagram.** Figure 1 provides an overview of the POETIC trial and participant flow process.

#### Registration and consent

Participating clinicians (GPs or nurse prescriber) will identify eligible patients during routine general practice consultations. The participating clinician will assess eligibility, provide potential participants with a verbal description of the trial, and if the patient is interested, will provide them with a comprehensive participant information leaflet (PIL). All potential participants will be given sufficient time to read the PIL, ask questions, and consider participation before being asked to provide informed consent. Women who consent to take part will be asked to sign a consent form, which will also be signed by the clinician who is taking consent. Copies of the consent form will be kept in the site file, and sent securely to the trial team in each centre.

All participating practices will be asked to keep an anonymous screening log of all ineligible and eligible but not consented/not approached patients. These will be used to detect any selection bias.

Participants will be informed that they have the right to withdraw consent for participation in the POETIC trial at any time and that their clinical care will not be affected at any time by declining to participate or withdrawing from the trial.

#### Inclusion criteria

Women aged 18 years and older presenting to primary care with at least one of three key urinary tract symptoms (dysuria, urgency including nocturnal and frequency that have been present for up to 14 days) and where the clinician suspects uncomplicated UTI will be eligible to take part. Patients should be able to provide written informed consent and be willing to complete the patient diary.

#### Exclusion criteria

Women with one or more of the following will not eligible for inclusion:Terminally illCurrently receiving treatment for life-threatening cancer (basal cell carcinoma, for example, excluded)Other severe systemic symptoms, such as high fever, renal angle pain, rigors.On long-term antibiotic treatment or have received antibiotics for urinary tract infection within the past four weeksHas had bladder surgery (including cystoscopy) within the past four weeksKnown or likely to have significant immune compromise (i.e. known immunodeficiency state, on long-term corticosteroid or chemotherapy treatment, insulin dependent diabetes)Known functional or anatomical abnormalities of the genitourinary tractHistory of pyelonephritisKnown pregnancyUnable to provide a urine sample on the day of first presentation

The clinician will need to ensure the participant provides a mid-stream urine (MSU) sample before leaving the practice. Patients can only be included in the POCT arm if the clinician is present to read the plate 24 hours later.

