### Data collection

#### Baseline case report form (CRF) – all participants

##### Eligibility

An eligibility CRF will be completed for all consented participants to ensure that they meet the eligibility criteria set out in the protocol. The clinician will then sign the form to confirm eligibility.

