##### Randomisation

The randomisation and allocation of eligible participants will be undertaken as part of the data collection process. Whilst completing the baseline CRF, clinicians will be asked to randomise the patient using a password protected POETIC randomisation website. Each practice will be allocated unique login details to the website. The clinician will enter the relevant data into the website, including the required stratifying and balancing variables, which include centre and practice details, and number of presenting symptoms (dysuria, frequency, urgency). The patient must present with at least one of these in order to be eligible for the trial. Once all relevant data has been entered, the randomisation programme will provide the trial allocation for that participant (either Standard care or POCT arm). This information will be recorded on the baseline CRF.

There is no credible blinding mechanism that can be utilised in this trial. Immediately after receiving the allocation, the clinician will need to be aware of the result of the randomisation so as to know whether to use the point of care test or not, and the participant will be need to made aware as they may need to receive a new prescription 24 hours after initial diagnosis, once the POCT results are made available to the clinician.

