### Analysis

#### Sample size calculation

A total of 614 participants (approximately 154 per network; 307 per arm) are required. We aim to improve appropriate antibiotic prescribing by at least 20% from an expected level of 55%. However, our sample size calculation is based on detecting a difference of 15 percentage points difference from control (i.e. from 55% to 70%). We need a total sample of 460 (230 for each arm) patients for final analysis (significance level α = 0.05, statistical power (1-β) = 0.90) and will recruit 614 patients to allow for a 25% loss to follow up (which requires a first urine and also follow-up via diary or telephone interview).

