#### Statistical analysis

The primary outcome will be appropriate antibiotic use on day 3 (with day 1 being the day that the patient consulted with their primary care clinician). For women who are shown to have a UTI, appropriate antibiotic use on day 3 will be defined as use of an antibiotic for which the isolated pathogen has been shown to have in vitro sensitivity (based on laboratory analysis). For women who do not have a UTI, appropriate antibiotic use on day 3 will be defined as no antibiotic use on this day.

The analysis of this primary outcome will be intention-to-treat and will be undertaken utilising a multi-level logistic regression. Whilst this is an individually randomised controlled trial we will use multi-level modelling with patient as the 1^st^ level and practice as the 2^nd^ level, plus we will test for clustering at the clinician level as the outcome could be seen as a clinician behavioural measure. Country will be used as a fixed level covariate at the practice level.

Secondary outcomes will be analysed using multi-level logistic or linear regression as appropriate, except for symptoms/recovery (daily symptom score), which will be modelled over time to allow for the correlation structure between scores on different days.

This trial is not powered for any sub-group analysis, and no interim analysis is planned. Some exploratory sub-group analysis will be done by country, number of symptoms and recent antibiotic history, using the relevant variables to form an interaction term with arm in the model.

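### The 24-hour plate-reading condition is written for the POCT arm only, so as worded it could act after randomisation and in one arm

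*Protocol article*

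**What the plan says.** The rule appears twice in the protocol article. Exclusion criteria, in the paragraph after the list: "Patients can only be included in the POCT arm if the clinician is present to read the plate 24 hours later". Trial intervention: "Patients can only be included in the POCT arm if the clinician/nurse is able to read the plate 24 hours later". The two sentences differ on who may read the plate, but both confine the condition to the POCT arm.

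On timing, the Eligibility section says that "An eligibility CRF will be completed for all consented participants to ensure that they meet the eligibility criteria set out in the protocol", and it comes before the Randomisation section. There, the clinician enters the stratifying and balancing data (centre and practice details, number of presenting symptoms), and then: "Once all relevant data has been entered, the randomisation programme will provide the trial allocation for that participant". The same section states that "There is no credible blinding mechanism that can be utilised in this trial".

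On analysis, the Statistical analysis section says: "The analysis of this primary outcome will be intention-to-treat".

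**The concern.** A condition for entering one named arm cannot be applied, as worded, until the arm is known. By then the woman has been randomised and the clinician knows her allocation. A woman who presents when nobody can read a plate the next day could stay in the trial if allocated to standard care. If allocated to POCT she would fail a stated condition of inclusion. The article does not say whether she is then dropped, managed and counted as standard care, or kept as allocated.

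Dropping or switching her would mean that the two groups no longer consist of all women as randomised. The loss would fall on one arm only, and an analysis plan cannot reliably restore women whom a practice has already left out. If those women differ in appropriate antibiotic use on day 3, the arm difference would be biased. If they do not, the cost is power alone.

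**Working it through.** **1. Can the condition act before allocation, as worded?**

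- The exclusions in the list apply to every woman. The plate-reading sentence stands outside that list and names one arm.
- The eligibility form comes before randomisation and checks the stated criteria. No stated criterion asks, for all women, whether a reader will be available.
- The variables named for the randomisation website do not include reader availability.
- The arm becomes known only from the website.

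Taken literally, then, the condition can act only after allocation and only in the POCT arm.

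**2. Do other safeguards cover it?** The screening log (Registration and consent) is for ineligible women and for eligible women not consented or not approached. It is not described as covering women already randomised. The 25% loss allowance (Sample size calculation) is defined by the first urine and by diary or telephone follow-up, not by unread plates.

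**3. The plan's own sample size.** Inputs from Sample size calculation: 55% versus 70%, "significance level α = 0.05", power 0.90. Two-sided testing is assumed, because the article does not state sidedness.

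- Mean rate = (0.55 + 0.70)/2 = 0.625.
- Uncorrected n per arm = [1.960 × √(2 × 0.625 × 0.375) + 1.282 × √(0.55 × 0.45 + 0.70 × 0.30)]² / 0.15² = 216.8.
- With continuity correction: (216.8/4) × [1 + √(1 + 4/(216.8 × 0.15))]² = 229.96, so 230 per arm and 460 in total.
- Loss allowance: 460/0.75 = 613.3, so 614.

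The stated figures reproduce, but only with the continuity correction (217 per arm without it). The power figures below use the same basis.

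**4. Power if POCT women are removed and not replaced (illustration).** The removed share is an assumption of 10% to 20%, which is about 31 to 61 of the 307 allocated to POCT. With n₁ = 230 controls and n₂ POCT women,

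power = Φ{[0.15 − ½(1/n₁ + 1/n₂) − 1.960 × SE₀] / SE₁},

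where SE₀ uses the pooled rate and SE₁ the two separate rates.

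| Removed | n₂ | Correction | SE₀ | SE₁ | Power |
|---|---|---|---|---|---|
| 0% | 230 | 0.0043 | 0.0451 | 0.0446 | 0.900 |
| 10% | 207 | 0.0046 | 0.0465 | 0.0457 | 0.883 |
| 20% | 184 | 0.0049 | 0.0481 | 0.0471 | 0.860 |

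**5. Bias (illustration).** Let f be the removed share and g the gap in appropriate use between the women kept and those removed. The full-arm rate is the kept rate minus f × g, so removal shifts the POCT rate by f × g. With an assumed g of 5 to 15 points:

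- low end: 0.10 × 5 = 0.5 points;
- high end: 0.20 × 15 = 3.0 points.

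If the gap is measured from the average of all women instead, the shift is f × g/(1 − f): 0.10 × 5/0.90 = 0.6 and 0.20 × 15/0.80 = 3.75 points. The design difference is 15 points. The shift favours POCT if the removed women have lower appropriate use and goes against it if they have higher use. If g is zero there is no bias.

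**The case against.** The strongest reply is that the sentence sits under Exclusion criteria, that a signed eligibility form precedes randomisation, and that a practice usually knows beforehand whether it will be staffed the next day. On that reading the check is made on every woman before the website is opened, and nobody is excluded after allocation. This is plausible and may be what was meant. It does not settle the matter: both sentences name one arm, one of them stands in the description of the intervention, and around 10 practices per centre will have to apply the rule as written.

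A second reply is that a condensed article may leave the handling of unread plates to the full protocol. That would answer an omission. Here a rule is stated, twice, in a form that fits badly with the randomisation and analysis sections.

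Several stronger readings are tempting, and the documents do not support them:

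- A reader might infer that the trial removes randomised women, so that the comparison is no longer a randomised one. The article nowhere says that an allocated woman is removed or moved, and the analysis section commits to intention-to-treat. The primary outcome does not need a read plate: it rests on laboratory culture of urine from both arms and on antibiotic use reported by diary or telephone. A woman with an unread plate can therefore still be analysed as allocated.
- A reader might infer that the urine-sample criterion has the same weakness. It does not. It excludes any woman unable to give a sample, in either arm, and a missing first urine is already part of the 25% loss allowance.
- A reader might take it as known that women presenting before a closed day differ in prescribing or severity. The article gives no evidence on this, so it remains an assumption, and the bias argument depends on it.

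**Conclusion.** The point holds as a defect of wording that could permit a one-sided exclusion or switch after allocation in an unblinded trial. It does not establish that randomised women will be lost. The two plate-reading sentences must be reconciled with the randomisation procedure and the intention-to-treat commitment.

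The size cannot be derived from the documents. Under the assumptions above, with nobody replaced, the power loss is 2 to 4 percentage points, which is modest. The possible bias, up to about a fifth of the 15-point target (3/15) or slightly more, is the greater worry, but it arises only if the women affected differ in appropriate antibiotic use. The correction is worth making before recruitment goes on, because it costs little and women left out at the practice cannot be reliably recovered at analysis.

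**What to change.** Replace both sentences with one eligibility criterion for all women: a trained clinician or nurse is available to read a plate about 24 hours later. Have it confirmed on the eligibility form, or as a required field on the randomisation page, before the allocation is released. State that every randomised woman stays in her allocated arm for the primary analysis whether or not the plate is read, and report unread plates in the POCT arm as non-adherence to the strategy.

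The cost is a short amendment and one additional field. Women who present when no reader is available the next day would be recruited to neither arm, so recruitment would be slightly slower. The targets of 460 evaluable and 614 recruited women do not change.

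### The 24-hour plate-reading condition is written for the POCT arm only, so read literally it permits exclusion after allocation in one arm of an unblinded trial

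*Protocol article*

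**What the plan says.** The condition appears twice in the protocol article. At the end of Exclusion criteria: "Patients can only be included in the POCT arm if the clinician is present to read the plate 24 hours later". In Trial intervention: "Patients can only be included in the POCT arm if the clinician/nurse is able to read the plate 24 hours later". Both sentences name the POCT arm, and they differ on who must read the plate. Every other inclusion or exclusion criterion applies to all women, and neither Control arm nor any other section sets an equivalent condition for standard care.

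The surrounding text bears on how the rule can operate:

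- Trial design: "POETIC is a two-arm, individual patient randomised controlled trial".
- Eligibility: "An eligibility CRF will be completed for all consented participants to ensure that they meet the eligibility criteria set out in the protocol". It carries the clinician's signature.
- Randomisation: "Once all relevant data has been entered, the randomisation programme will provide the trial allocation for that participant (either Standard care or POCT arm"). The same section adds: "There is no credible blinding mechanism that can be utilised in this trial".
- Statistical analysis: "The analysis of this primary outcome will be intention-to-treat".

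The article does not say that plate-reading cover is confirmed for every woman before she is randomised. It also does not say what happens to a woman allocated to POCT when nobody can read her plate.

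**The concern.** An eligibility condition protects a randomised comparison only if it is applied before allocation and to everyone. A condition on membership of one arm cannot be applied before the arm is known. Here that moment comes when the website returns the allocation, and the person applying the condition then knows the result.

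Take a consultation with no next-day reader, for instance before a weekend. If the woman is allocated to standard care, nothing in the text affects her. If she is allocated to POCT, the text says that she cannot be included in that arm and gives no next step. If a site took this to mean that she is not in the trial, the POCT arm would lose a subset of women whom the control arm keeps. Should that subset differ in case mix or prescribing, the difference would enter the estimated effect, and analysis could not reliably remove it. The screening log described under Registration and consent covers ineligible women and eligible women who were not consented or approached. It would not clearly capture a consented, randomised woman who was excluded afterwards.

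**Working it through.** **1. The plan's own figure.** Inputs from Sample size calculation: 55% versus 70%, α = 0.05 (two-sided assumed, as sidedness is not stated), power 0.90, 25% loss.

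- Uncorrected: n = [1.96·√(2·0.625·0.375) + 1.2816·√(0.55·0.45 + 0.70·0.30)]² / 0.15² = 216.8 per arm.
- Continuity-corrected: (216.8/4)·[1 + √(1 + 4/(216.8·0.15))]² = 229.96, so 230 per arm and 460 in total.
- Recruitment: 460/0.75 = 613.3, so 614.

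The stated 230, 460 and 614 are reproduced exactly and are not in dispute.

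**2. What cannot be computed.** The bias depends on the share *f* of POCT allocations excluded and on how far those women's appropriate-use rate differs from that of the others. The documents give neither, so what follows is illustration only.

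**3. Illustrative bias.** Assume no true effect, a control rate of 55%, and excluded women whose rate is *g* below that of the remaining women. Control keeps all women, so its rate is 0.55. The women remaining in POCT have rate 0.55 + *f·g*. The spurious difference is *f·g*, with 230 versus 230(1 − *f*) women analysed. The rejection probability comes from the two-sided two-proportion z-test without continuity correction, ignoring clustering.

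| *f* | *g* (points) | Spurious difference (points) | Type I error |
|---|---|---|---|
| 5% | 10 | 0.5 | 0.051 |
| 5% | 20 | 1.0 | 0.055 |
| 10% | 10 | 1.0 | 0.055 |
| 10% | 20 | 2.0 | 0.070 |
| 20% | 10 | 2.0 | 0.069 |
| 20% | 20 | 4.0 | 0.129 |
| any | 0 | 0 | 0.050 |

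Worked case, *f* = 20% and *g* = 20 points: 55% versus 59% with 230 versus 184 women.

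- Pooled rate: (230·0.55 + 184·0.59)/414 = 0.568.
- Null standard error 0.0490; alternative standard error 0.0489.
- Φ((0.04 − 1.96·0.0490)/0.0489) + Φ((−0.04 − 1.96·0.0490)/0.0489) = 0.126 + 0.003 = 0.129.

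With the continuity-corrected test, the two rows at *f* = 20% become about 0.056 and 0.108. A rate that is higher rather than lower among the excluded women would reverse the sign. The documents support neither direction.

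**4. Power if women are excluded.** At *f* = 20%, 307·0.2 ≈ 61 POCT allocations are lost and 230·0.8 = 184 remain for analysis. Power for 55% versus 70% falls from 0.900 to 0.860 (continuity-corrected), or from 0.916 to 0.882 (uncorrected).

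**5. Power if women are retained as allocated.** If intention-to-treat keeps the same 20% in POCT and they get no benefit from the test (assumed), the difference becomes 0.8·15 = 12 points. Power at 230 per arm is then about 0.72 (continuity-corrected). This is dilution from non-adherence and does not produce false positives.

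**The case against.** The strongest defence is that the sentence is only loosely worded. It stands in the eligibility section, beside the requirement to obtain a urine sample before the woman leaves. Eligibility is assessed before consent and signed off on a CRF for all consented participants, and the Randomisation section speaks of allocating eligible participants. A clinician who cannot know the arm in advance can honour the rule only by not recruiting when nobody can read a plate. On that reading the arms stay balanced, and the women concerned appear in the screening log as ineligible. A condensed article may also omit a check that the full protocol or the CRF contains.

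Much of this stands. A reader might infer that women allocated to POCT are dropped or switched, that the arms are therefore not comparable, or that the plan contradicts its own intention-to-treat commitment. The documents do not support any of these. No section orders exclusion or transfer, and intention-to-treat would keep a woman with an unread plate in her allocated arm.

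The defence does not remove the wording. The CRF checks criteria as the protocol sets them out, and this one is limited to a single arm both times it appears. That is text the article states, so condensation does not explain it. Intention-to-treat also does not help if a site treats a woman as never included.

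The difference between clinician and clinician/nurse is minor, since participating clinicians are defined as GPs or nurse prescribers. It is simply worth aligning.

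**Conclusion.** The point holds as a risk that the wording permits. A one-arm inclusion condition, in an individually randomised trial where the arm is known only after allocation to an unblinded clinician, can act literally only as a post-randomisation exclusion in that arm. Such an exclusion would conflict with the intention-to-treat analysis. Whether any site would apply it that way cannot be told from the article.

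The size is unknown. Across the assumed ranges (5% to 20% excluded, 10 to 20 points lower) the type I error moves from practically nominal to about 0.13. At shares of 10% or less it stays at or below about 0.07, and there is no bias if the affected women are like the rest. Loss of power from exclusion alone is modest. The sample size stands. The point should be fixed because the remedy is simple and the damage, if it occurred, could not be reliably repaired in analysis.

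**What to change.** Replace both sentences with one eligibility criterion for every woman: trained staff are available to read a plate about 24 hours after this consultation. Use the same description of who reads the plate in Trial intervention and in Exclusion criteria. Confirm the criterion on the existing eligibility CRF before the randomisation website is opened, so that women seen without next-day cover are logged as ineligible whichever arm they might have received.

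Add to Statistical analysis that every randomised woman is analysed in her allocated arm whether or not a plate was read, and that unread plates are reported as non-adherence.

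The cost is a wording change and one item on a form already in use. The real downside is that neither arm can recruit on days without next-day cover, which may slow accrual.
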